# Study protocol: a multi-center, double-blind, randomized, 6-month, placebo-controlled trial to investigate the effect of supplementing hormone therapy FET cycles with Gushen’antai pills on the outcomes of in vitro fertilization

**DOI:** 10.1186/s13063-021-05614-w

**Published:** 2021-09-26

**Keywords:** FET, Hormone therapy, TCM, Randomized controlled trial, Ongoing pregnancy rate

## Abstract

**Background:**

Infertility is a widespread global challenge. Currently, the most effective treatment strategy for infertility is in vitro fertilization (IVF), which is an assisted reproductive technique (ART). The use of IVF for assisted pregnancy dates back to the last 41 years when the first IVF baby was born. During IVF, many oocytes are obtained in an IVF cycle, and more than one embryo is formed. Subsequently, frozen-thawed embryo transfer (FET) is increasingly being used in IVF cycles for women in whom a fresh embryo transfer fails to result in a pregnancy, or in those who return for a second baby. However, the pregnancy success rates following FET treatment cycles are reportedly lower than in fresh embryo transfers. Therefore, recent related studies are increasing determining mechanisms of improving the sustained pregnancy rate of FET and reducing the rate of early abortion.

The Gushen’antai pill (GSATP), which contains a mixture of 10 herbs, has been widely used in traditional Chinese medicine (TCM) as a pharmacological option to prevent miscarriage. However, randomized controlled trials (RCT) have never been conducted to provide high-level clinical evidence on the clinical efficacy of GSATP. The objective of this study is to investigate the effect of GSATP of hormone therapy (HT) FET cycles on pregnancy rate.

**Methods:**

A total of 300 subjects aged between 18 and 40 years which prepared for HT cycle FET will be enrolled in the study. The patients were from five different hospitals, with 60 patients from each hospital. Patients were randomly divided into two groups, and medication was started on the day of endometrial transformation. After FET 28 days, B-ultrasound was done to determine whether to continue the medication. Baseline assessments were carried out before the trial and outcomes were collected 4, 6, 8, 10, and 12 weeks of each gestational cycle.

**Discussion:**

Differences in ongoing pregnancy rate, clinical pregnancy rate, implantation rate, and threatened abortion rate between the two groups will be statistically analyzed. We can finally have an objective evaluation of the efficacy of the traditional Chinese medicine Gushen’antai pills.

**Trial registration:**

ChiCTR1900026737. Registered October 20, 2019.

## Background

Infertility is a global challenge estimated to affect between 8 and 12% of couples in childbearing age worldwide [1]. Being an effective treatment, IVF, an ART has been widely used for the last 41 years since the first IVF baby was born in 1978. Previously, IVF was mainly done by the transfer of fresh embryos. In recent years, however, FET has increasingly gained importance in IVF protocols [2].

With the increasing number of FET cycles, an assessment of the best endometrial preparation is primary to maximizing the success rate of ART [3]. Also, FET helps to maximize the cumulative pregnancy rate per oocyte retrieval. Previous clinical studies have reported that the pregnancy rate in FET cycles is lower than fresh IVF/ intracytoplasmic sperm injection (ICSI) cycles [4]. However, the latest large retrospective cohort study found no significant difference between FET cycles and fresh cycles [5]. Besides, the increasing concerns on the adverse effects of controlled ovarian stimulation (COS) on the endometrial and uterine environment have increased the popularity of FET [6]. Current studies have mostly focused on different cycle regimens, such as natural cycles and HT cycles, for the endometrial preparation of FET [7]. While the natural ovulatory cycles are spontaneous, HT cycles use estrogen and progesterone hormones to prepare endometrium and are, therefore, more precise.

Although the results of a meta-analysis revealed that the type of estrogen supplementation and the route of administration do not affect the success rate of FETs [8], the effect of administration route and dose of progesterone is still controversial [9, 10]. Interestingly, no efficiency and safety differences between natural cycle FET and HT cycle FET could be found by a meta-analysis [11], which was also proven in another study [7, 12]. In a study performed by Givens et al., higher miscarriage rates were found in the HT cycle FET group, and there was also no difference between the live birth rates [13].

Gushen’antai pills (GSATP) are processed by TCM and are a classic prescription with modern pharmaceutical technology. The pill is a mixture of 10 herbs and has been widely used as a pharmacological option in China for preventing miscarriage [14, 15]. Notably, GSATP is approved by the Chinese State Food and Drug Administration (SFDA). According to the theory of TCM, a full kidney Qi is representative of strong reproductive ability, while the kidney Qi is exuberant and thus to keep the mother and fetus in a stable state. The GSATP is mainly used for tonifying the kidney, and the herbal components are mutually reinforcing. The pill is made up of ten kinds of precious Chinese herbal medicines (*Polygonum multiflori*, *Rehmannia glutinosa*, *Cistanche deserticola*, *Tripterygium wilfordii*, *Tripterygium wilfordii*, *Radix Atractylodes*, *Radix macrocephala*, *Radix Scutellariae*, *Radix Paeoniae*, *Rubra*, *Chinese dodder seed*, *Uncaria*, and *Mulberry Parasitoids*) through long-term clinical practice and optimized compatibility. According to the TCM theory, GSATP prevents miscarriage. The safety of TCM can be improved through strict syndrome differentiation and deep processing [16], and it is what GSATP pursues and do. No adverse drug reaction (ADR) has been reported during the many years of GSATP use.

Improving the success rate of the HT cycle FET is a complex process that has not yet been fully investigated. Therefore, multi-target therapy, such as TCM, may offer unique advantages in this complex disease treatment over the single-target use prevalent in western medicine [17].

Although the response of GSATP in patients is excellent, the lack of high-quality, evidence-based medicine restricts its widespread use. The combination of evidence-based medicine, modern medicine, and TCM is an exciting field that has continuously attracted immense attention and efforts [18]. Therefore, a large multi-center, double-blind, randomized, placebo-controlled trial should be conducted to develop a simple, inexpensive, and widely practical oral medication treatment based on GSATP.

### Aims

#### The primary objective and secondary objectives

The primary aim of this trial is to evaluate and verify the clinical efficacy of GSATP, and its effect on the ongoing pregnancy rate (OPR) of HT FET cycles. The secondary objectives are to determine whether GSATP affects implantation rate (IR), clinical pregnancy rate (CPR), and threatened abortion rate (TAR) of HT cycle FETs.

## Methods

### Diagnostic criteria

The GSATP is suitable for early threatened abortion (TA), which belongs to kidney yin deficiency in TCM. Early TA refers to the premonitory abortion within 12 weeks of pregnancy, which is mainly characterized by a small amount of vaginal bleeding, paroxysmal lower abdominal pain or low back pain, unopened cervical opening, undamaged fetal membrane, and the size of the uterus is consistent with the gestational week [19]. Kidney yin deficiency syndrome in TCM can be diagnosed as long as the waist and knees are sour and soft and any other one of the following symptoms: falling pain in the lower abdomen, or accompanied by dizziness and tinnitus, dry mouth and dry throat, mental fatigue, and feverish palms and soles.

### Recruitment

We recruited participants who purposed to do FET from reproductive centers in five different tertiary hospitals: Affiliated Hospital of Shandong University of Traditional Chinese Medicine, Maternity and Child Health Care of ZaoZhuang, Shanxi Maternal and Child Health Care Hospital, The First Affiliated Hospital of Wenzhou Medical University, and Jinan Military General Hospital. These five hospitals are all tertiary A public hospitals and have the qualification of IVF-FET, recruiting 60 patients in each hospital. In order to ensure the consistency of the procedures in all the sites, the training was uniformly conducted before the start of the trial. During the trial, all the sites communicated in a timely manner through the network, and the progress was regularly checked by professionals to ensure the consistency and uniformity of the trial. This study was conducted according to the Declaration of Helsinki and approved by the Reproductive Medicine Ethics Committee of the Affiliated Hospital of Shandong University of Traditional Chinese Medicine (approval number 20191109). Written informed consent was obtained from patients before study enrollment. Prospective baseline data of patients were collected, including height, weight, basic endocrine level, and detailed IVF process record. Informed consent was obtained from the patients before any study procedures were done. We estimate that it will take about six months to complete this phase of the test. A study flow chart is displayed in Fig. 1.

**Fig. 1 Fig1:**
[figure not shown]
Study flow chart

### Inclusion criteria

Patients who met the following inclusion criteria were included in the study:
①Age: 22–40 years old②Patients who had two or more high-quality transplantable frozen fetuses③Patients who received HT cycle FET④Patients who had less than three previous FET cycles, ≤two unexplained abortions, ≤ two implant failures⑤Patients who have not received similar drug treatment⑥Patients who have no history of mental illness and have no abnormality in liver and kidney function and electrocardiogram

### Exclusion criteria

The following was the exclusion criteria used in this study:
①BMI ≥ 30 kg/m^2^②Patients with abnormal development of the reproductive system and one abnormal chromosome karyotype of both male and female③Patients with major systemic diseases④Patients with endometriosis, adenomyosis, and hydrosalpinx⑤Patients with previous endometriosis

### Allocation concealment mechanism

Participants were randomly assigned to either the control group or the experimental group, at a proportion of 1:1 according to the computer-generated random schedule in R software by an assessor who was blinded to the treatment allocation. Assignment concealment was guaranteed because our experiment identified the subjects from the start of the test. The uncertainty of subjects can fully guarantee the effect of allocation concealment.

Clinical recovery was evaluated by an assessor who was blinded to the treatment allocation. The assessor was comprehensively trained before the study was done. Because of the professionalism of the medical profession, neither the participants nor the staff was assigned blindly and naturally, but the distribution of the participants was not disclosed in subsequent evaluations. Patient-related information such as OPR, CPR, IR, and TAE was collected by personnel who were not directly involved in the experiment. The doctors only collected the information at the end of the trial.

### Potential risks and handling

Although GSATP has a safe history of pharmacological use, we do not rule out that its use could cause some side effects. At present, the commonly reported adverse reactions of TCM use mainly include gastrointestinal reactions, liver, and kidney damage. Subsequently, patients were well informed of the potential risks in advance.

### Patient and public involvement

Patients are neither involved in the development of research issues nor in the design and recruitment of research. However, patients participated in the study and were randomly divided into two groups, taking GSATP and placebo respectively. The cost of the drugs used in this study is borne by the research group, and the patients have no part of their own expenses.

The results of the study will be disseminated to participants and their families through WeChat notifications, patient organization platforms, and public information meetings

### Interventions

A randomized, double-blind control method was used to select eligible patients according to the ratio of 1:1 between GSATP and placebo. The GSATP (Product specification: 6 g* 9 bags) and placebo (starch as an ingredient, without the active ingredients) were obtained from Beijing bran Pharmaceutical Inc and re-labeled by Beijing bran Pharmaceutical Inc, according to the national drug standards of the State Food and Drug Administration of China. In this paper, the application research of GSATP in the treatment of threatened abortion is consistent with the indications in its published instructions.

The routine dose of GSATP (6 g tid) or placebo (6 g tid) was orally administered to patients four hours before the endometrial transformation. We ask patients to take their medicine on time every day. Clinical pregnancy was confirmed by interpreting B-ultrasound results 28 days after FET. Oral administration of the treatment on pregnant women was continued until 12 weeks of pregnancy, but drug administration was not done on patients who had not conceived. Patients with ectopic pregnancy were included in adverse events. Both doctors and patients were blinded to the identity of the syringe contents. Patients were allowed to use other drugs in case of emergency, but data from such patients were not included in the statistical analysis.

Adherence reminder sessions were done during the initial product dispensing and at each follow-up visit. The following was communicated to the patients beforehand: the importance of adhering to the daily study product instructions, including the time taken, the importance of storing the study drug appropriately and making the entire study drug, and the measures to be taken in case of missed doses. One of our staff regularly contacted the patients via WeChat to enquire about the medication.

### Safety assessment

All subjects were managed and followed up by medical personnel including the chief physician during medication. Follow-up was performed in the outpatient department at weeks 2, 5, 7, 9, and 10 after FET to record any local and/or systemic reactions during medication and any adverse events throughout the study. Due to the wide range of targets for TCM, potential beneficial or adverse reactions in patients will also be recorded during each follow-up visit. All local and systemic adverse events, regardless of their severity, will be recorded. Once any adverse reaction occurs during medication, the drug will be stopped immediately and medical personnel will observe and deal with it according to the condition. The patient's questionnaire was used to collect data on other medication-related symptoms.

### Outcome measures

The primary endpoint was OPR at week 12 of pregnancy. The secondary endpoints were IR, CPR, and TAR. The OPR, IR, CPR, and TAR were measured at the end of the experiment. Hormone levels were monitored and recorded at FET on days 1, 7, and 14. IR (%) = number of implantation gestational sac/number of transferred embryo × 100%, CPR(%) = number of clinical pregnancy/number of transfer cycle × 100%, OPR(%) = number of continuous pregnancy/number of transfer cycle × 100%, and TAR(%) = number of abortion/number of clinical pregnancy × 100% (Table 1).

**Table 1 Tab1:** Checklist of items for reporting trials of Chinese herbal medicine formulas

Section/topic	Item number	Standard CONSORT checklist item	Extension for CHM formulas	Reported on page number
**Title, abstract, and keywords**	1a	Identification as a randomized trial in the title	Statement of whether the trial targets a TCM pattern, a Western medicine-defined disease, or a Western medicine-defined disease with a specific TCM pattern, if applicable	1–4;19–49;52
	1b	Structured summary of trial design, methods, results, and conclusions (for specific guidance, see CONSORT for abstracts [26, 27])	Illustration of the name and form of the formula used, and the TCM pattern applied, if applicable	39–45;86–94
	1c		Determination of appropriate keywords, including “Chinese herbal medicine formula” and “randomized controlled trial”	52

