### Statistical analysis

#### Sample size

The sample size was calculated based on a primary study [20], that revealed the rate of ongoing pregnancy in the observation group was significantly higher than that of the control group (63.83% VS 42.86%, *x*^2^=4.24, *P*< 0.05). An estimated OPR of 0.6 was obtained. According to 1:1 ratio, 65% efficacy of GSATP, *α*=0.05 and *β*=0.2, there were 130 patients in the treatment group and 130 in the placebo group. Considering the complexity of clinical practice, the loss rate is estimated to be 0.1. Finally, the sample size was calculated to be 300 subjects.

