#### Analysis

The study data were collected and managed by non-clinical staff who were responsible for data management in each clinical center. The data were shown as follows: continuous variables with normal distribution were presented as means±SD, and the count data are presented in the form of n (%). Statistics were run using SPSS version 21 software (SPSS, Inc., Chicago, IL). The differences between the two groups were detected using *χ*^2^ for counting data or t test used for comparative analysis of measuring data. *P* values of less than 0.05 were considered to be statistically significant.

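### The implantation rate is counted per embryo but compared by plain chi-square; if some women receive more than one embryo and their outcomes are positively correlated, its type I error exceeds 5%

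*Protocol article*

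**What the plan says.** **Unit of randomisation.** The section on the allocation concealment mechanism says: "Participants were randomly assigned to either the control group or the experimental group, at a proportion of 1:1". The participant is the woman.

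**Endpoint.** Under Outcome measures: "The secondary endpoints were IR, CPR, and TAR". The implantation rate (IR) is given as "IR (%) = number of implantation gestational sac/number of transferred embryo". The same paragraph defines the clinical pregnancy rate (CPR) as "number of clinical pregnancy/number of transfer cycle", and the ongoing pregnancy rate (OPR) has the same denominator. The counting unit therefore changes to the embryo for IR. The abstract lists IR among the outcomes whose group difference will be analysed statistically, so it is meant to be tested and not only described.

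**Test.** The Analysis section names chi-square "for counting data or t test used for comparative analysis of measuring data", and "values of less than 0.05 were considered to be statistically significant". It names no other method. The CONSORT table marks additional and adjusted analyses as not applicable.

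**Embryos per woman.** The inclusion criteria require at least two good-quality frozen embryos to be available. The article does not say how many are transferred.

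**The concern.** IR as printed is a ratio of two counts, so the Analysis section sends it to the chi-square test. That test assumes independent units. Two embryos placed in the same woman share a uterus, an endometrial preparation and a pair of parents, so one would expect their outcomes to be positively correlated. If they are, two embryos from one woman carry less information than two embryos from two women. The test does not know this: its variance is too small and its P value too low. At stake is a false claim that the treatment improves implantation, on a named secondary endpoint of a trial meant to provide high-level evidence.

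**Working it through.** **Inputs from the article.** Women are randomised 1:1 (Allocation concealment mechanism). The IR denominator is embryos transferred (Outcome measures). The test is chi-square at 0.05 (Analysis). The sides are not stated; I take chi-square as two-sided.

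**Inputs assumed, because the article gives none.** The within-woman correlation of implantation, ρ, is taken as 0.05 to 0.5. The share of women who receive two embryos, *f*, is taken as 0, 0.5, 0.8 or 1, with the rest receiving one.

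**Step 1: the stated level under independence.** With ρ = 0, or with one embryo per woman, the size is 2 × [1 − Φ(1.96)] = 5.0%. This is the level the plan intends.

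**Step 2: variance inflation.** With *m* embryos per woman, the variance of the pooled proportion is multiplied by

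DE = 1 + ρ × (Σm² / Σm − 1).

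- *f* = 1: Σm²/Σm = 4/2 = 2, so DE = 1 + ρ.
- *f* = 0.8: (0.8 × 4 + 0.2 × 1)/(0.8 × 2 + 0.2 × 1) = 3.4/1.8 = 1.889, so DE = 1 + 0.889ρ.
- *f* = 0.5: 2.5/1.5 = 1.667, so DE = 1 + 0.667ρ.
- *f* = 0: DE = 1.

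**Step 3: true size of the nominal 5% test.** Size = 2 × [1 − Φ(1.96/√DE)]. For example, with *f* = 1 and ρ = 0.3, DE = 1.3, 1.96/1.140 = 1.719, and the size is 8.6%.

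| ρ (assumed) | all two embryos | 80% two | 50% two | all single |
|---|---|---|---|---|
| 0.05 | 5.6% | 5.5% | 5.4% | 5.0% |
| 0.1 | 6.2% | 6.0% | 5.8% | 5.0% |
| 0.2 | 7.4% | 7.1% | 6.6% | 5.0% |
| 0.3 | 8.6% | 8.2% | 7.4% | 5.0% |
| 0.5 | 11.0% | 10.3% | 9.0% | 5.0% |

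The formula does not involve the number of women.

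**Step 4: simulation check.** Beta-binomial data were simulated with two embryos each, 130 or 150 women per arm (the article's 130 per group, or 300 in total), assumed IR of 35% or 45%, and 40,000 trials per setting. The uncorrected test rejected in 4.8% to 5.3% of trials at ρ = 0. At ρ = 0.1 it rejected in 5.8% to 6.5%, and at ρ = 0.5 in 10.6% to 11.6%. The excess therefore comes from the clustering.

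**Step 5: continuity correction.** The article does not say whether one is used. With 135 women per arm, assumed IR 40% and two embryos each (60,000 trials), the continuity-corrected test rejected in 4.0%, 5.1%, 6.2%, 7.3% and 9.3% of trials at ρ = 0, 0.1, 0.2, 0.3 and 0.5. The correction hides the problem at low correlation and does not remove it at higher values.

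**The case against.** **The size is unknown.** The eligibility rule concerns embryos available, not embryos transferred, and no correlation is given. With single transfers throughout, the problem is nil. At ρ = 0.05 the excess is about half a percentage point, and a continuity correction would absorb the excess at ρ = 0.1. All of this stands. A reader might infer that the test certainly breaches 5%, or breaches it badly; the article does not support either. Some multiple transfer is still the more natural reading: every eligible woman has at least two embryos, no single-transfer rule is stated, and separate embryo and cycle denominators are kept, which would be nearly redundant if every cycle used one embryo.

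**The analysis plan may handle it.** The Analysis section is one general sentence in a condensed article and does not name IR. But it does state a test for counts, and IR as printed is a count ratio. This is a stated rule that fits badly, not detail left to another document.

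**The reach is narrow.** This also stands. IR is one of three secondary endpoints. A reader might extend the point to the primary endpoint, but OPR and CPR are counted per transfer cycle. Nor can one say that the plan's confidence interval for IR is too narrow, because the article specifies none; the only mention is standard checklist wording.

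**Conclusion.** The concern holds in conditional form. For IR, the stated test ignores that embryos are nested in the randomised women. Its true type I error is above 5% if two things are true: some women receive more than one embryo, and implantation within a woman is positively correlated. The direction follows from the stated method under those conditions. The size rests wholly on assumed values: about 5.6% to 11.0% with two embryos each for correlations of 0.05 to 0.5; for correlations of 0.1 to 0.5, about 6.0% to 10.3% if 80% of women have two and 5.8% to 9.0% if half do; and 5.0% if all transfers are single. The excess is small at the low end and matters from a correlation of roughly 0.2 upward. It is worth correcting, but it does not threaten the trial's main conclusion.

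**What to change.** Keep the printed IR formula as the estimate in each arm, and replace the embryo-level chi-square for IR with an analysis that takes the woman as the unit. Two options fit:

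- a GEE on embryos with identity link, independence working correlation and robust standard errors clustered on the woman; or
- a bootstrap of the ratio of sacs to embryos that resamples women within arm.

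Report the difference in IR with a 95% CI. The details matter. A logistic link would give an odds ratio rather than a difference. With unequal numbers of embryos, an exchangeable working correlation can reweight women, so the estimate need not match the printed ratio. The independence form with treatment arm as the only covariate reproduces the ratio exactly. It would also help to state how many embryos may be transferred.

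The cost is a short addition to the Analysis section. No extra patients are needed, and no data beyond sac and embryo counts per woman. The standard error for IR grows by √DE: with two embryos each, about 5% at a correlation of 0.1 (√1.1 = 1.049) and about 22% at 0.5 (√1.5 = 1.225), with a correspondingly larger P value. If every transfer proves to be single, the result is essentially unchanged.

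### The primary ongoing pregnancy rate is divided by transfer cycles, so women randomised and dosed but never transferred drop out of the comparison

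*Protocol article*

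**What the plan says.** All references are to the protocol article.

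- **Endpoint.** Outcome measures states: "The primary endpoint was OPR at week 12 of pregnancy". The same section gives the formula "OPR(%) = number of continuous pregnancy/number of transfer cycle". CPR is also divided by transfer cycles.
- **Unit randomised.** Allocation concealment mechanism: "Participants were randomly assigned to either the control group or the experimental group, at a proportion of 1:1".
- **Unit of sizing.** Sample size plans 130 patients per group, allows for 10% loss, and ends: "Finally, the sample size was calculated to be 300 subjects".
- **Start of drug.** Abstract, Methods: "medication was started on the day of endometrial transformation". Interventions: treatment is "orally administered to patients four hours before the endometrial transformation". The two descriptions are not worded alike, but both put the first dose before the embryo transfer.
- **Test.** Analysis compares counts between the two groups by chi-square.

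The article names no analysis that keeps every randomised woman in the denominator. Interventions separately removes from the analysis women who used other drugs in an emergency.

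**The concern.** Randomisation makes the two arms comparable as whole groups of women. The stated denominator replaces those groups with the women who reached transfer. Whether a woman reaches transfer is settled after she has been randomised and has started drug; a cycle may be cancelled, for example, or the embryos may not survive thawing. Such a woman is not counted as a failure under the formula. She is not counted at all.

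Two things are at stake. If non-transfer is equally common in both arms, each rate overstates what a woman starting treatment can expect, and any true difference is overstated by the same factor. If non-transfer differs between the arms, the comparison itself is biased, and the arm that loses more women looks better.

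This is not a detail left to an analysis plan. The article fixes the denominator of its primary endpoint. Naming an all-randomised analysis set later would not repair it, because a rate per transfer cycle still omits women without a transfer.

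**Working it through.** **1. Who is in the formula.** A woman with a transfer is in the denominator, and in the numerator if the pregnancy is ongoing at week 12. A woman randomised and dosed without a transfer is in neither. Drug starts before transfer and randomisation must precede drug, so such women can exist.

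**2. The plan's own figure.** The text does not state which two rates were compared. Reading them as 0.60 v 0.4286, with two-sided α = 0.05 and 80% power, the unpooled formula gives

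n = (1.96 + 0.842)² × (0.60×0.40 + 0.4286×0.5714) / (0.60 − 0.4286)² = 129.6, or 130 per arm.

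This matches the stated 130 per arm; a pooled-variance formula gives 133. The allowance for loss gives 260/0.9 = 289, and the stated 300 equals 5 hospitals × 60. The sizing therefore rests on 260 evaluable women, and 300 is the total after the allowance.

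**3. Null comparison, cancellation rates assumed.** Take 150 women per arm and a true ongoing rate of 0.50 per randomised woman in both arms. With cancellation c, the per-transfer rate is 0.50/(1 − c).

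| Cancellation (arm A v arm B) | Per-transfer OPR | False difference |
|---|---|---|
| equal, c in both | both 0.50/(1 − c) | 0 |
| 2% v 5% | 51.0% v 52.6% | 1.6 points |
| 5% v 10% | 52.6% v 55.6% | 2.9 points |
| 0% v 10% | 50.0% v 55.6% | 5.6 points |

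In whole women, the second row is 3 v 8 untransferred: 75/147 = 51.0% v 75/142 = 52.8%, a difference of 1.8 points.

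A two-sided 5% test (normal approximation) then rejects in about 7.8% of trials for 5% v 10%, and about 15.6% for 0% v 10%.

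**4. Planning rates, equal cancellation assumed.** Take 0.60 v 0.4286 as per-transfer rates and multiply by (1 − c). Power is at 150 per arm with no other loss; n is from the pooled formula.

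| c | Women per arm not transferred | Per-randomised OPR | Power | n per arm for 80% |
|---|---|---|---|---|
| 0 | 0 | 0.600 v 0.429 | 84.7% | 133 |
| 2% | 3 | 0.588 v 0.420 | 83.2% | 138 |
| 5% | 7.5 | 0.570 v 0.407 | 80.9% | 147 |
| 10% | 15 | 0.540 v 0.386 | 76.7% | 163 |

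At c = 10% the difference per randomised woman is 15.4 points, against 17.1 per transfer.

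**The case against.** **The size is unknown and may be small.** The article reports no cancellation or thaw-failure rate. Drug starts only at endometrial transformation, and the trial is described as double-blind and placebo-controlled, so there is no evident reason for non-transfer to differ by arm. If the pill affects neither pregnancy nor the chance of transfer, losses differ only by chance and a null comparison stays null. Even the 2% v 5% case gives under 2 points, against about 17 points on the planning rates as read above. All of this stands, and it is why confidence is moderate. It does not make the denominator sound: drug is taken before transfer, so equal loss is an assumption that the stated formula relies on without need.

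**The 10% loss allowance could absorb these women.** It can for precision. It does nothing about bias.

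**Three stronger readings are tempting, and the article does not support them.**

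- A reader might infer that a woman can be counted more than once, because the unit is a cycle, because each woman has at least two frozen embryos, and because the Abstract says "outcomes were collected 4, 6, 8, 10, and 12 weeks of each gestational cycle". No section plans a second transfer. Interventions says "drug administration was not done on patients who had not conceived", Safety assessment gives a single visit schedule after FET, and the sizing counts subjects. The Abstract phrase follows a list of gestational weeks and is loose wording about pregnancy follow-up. Two embryos are equally compatible with one transfer of both. The article reads as one cycle per woman, so no argument about repeated or dependent observations follows.
- A reader might infer that allocation is abandoned. Nothing moves women between arms; the formula narrows each arm.
- A reader might infer that the sizing requires 300 analysed women. It requires 260.

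**Conclusion.** The point holds for the denominator. As written, OPR and CPR leave out women who were randomised and dosed but not transferred, and they do so by a stated rule.

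The size rests entirely on assumed cancellation. Over the range shown, with equal true rates of 50% per randomised woman, the false difference runs from zero (equal cancellation) to 5.6 points (0% v 10%). Equal cancellation of 2% to 10% overstates each rate by a factor of 1.02 to 1.11, from 1/0.98 to 1/0.90. The power figures also depend on reading the planning pair as 0.60 v 0.4286. The change should be made because it concerns the primary endpoint and is cheap. The article gives no ground for saying that a large bias is likely. Confidence: moderate.

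**What to change.** In Outcome measures, redefine the primary OPR as the number of women with an ongoing pregnancy at week 12 from the first FET cycle after randomisation, divided by all women randomised to that arm. A woman with no transfer in that cycle counts as having no ongoing pregnancy. Define CPR in the same way, with clinical pregnancy in the numerator. Report per-transfer rates as supportive only, together with the number randomised but not transferred in each arm. The words on the first FET cycle are clarification; they change nothing if each woman has one cycle.

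The cost is wording and slightly lower stated rates; no extra visits or procedures are needed. If the planning rates are per transfer, some power is lost as well. At 10% cancellation, 135 transferred women per arm would still exceed the 133 needed per transfer, while power per randomised woman at 150 per arm is 76.7%. At 5% or less it stays above 80%, if there is no other loss. The sponsor should state the cancellation rate it expects and say whether the planning rates are per transfer or per woman.
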